### Data management and confidentiality

Study data generation at the study sites is clearly separated from data storage, processing and statistical analysis in the Department of Medical Statistics, Informatics and Health Economics. This requires a validated database system programmed in a customized software package, which is provided at the same place. The system includes an audit trial facility and will be used for defining the database structure, data entry, for handling data cleaning processes, and for final storing of the data. The evaluation of the data takes place by double-entry of the data and manual/visual evaluation of plausibility. The database will be closed at the completion of the study after entry of all collected data and clarification of all queries. All study findings and documents will be regarded as confidential. The investigator and members of the research team must not disclose any information without prior written approval from the Sponsor. The pseudonymity of patients participating must be maintained. Throughout documentation and evaluation, the patients will be recognized on case report forms (CRFs) and other documents by age and identification number. Documents that identify the patient personally (e.g., the signed informed consent form) must be maintained in confidence by the investigator. The patients will be told that all study findings will be stored on computer and handled in strictest confidence.

### Sample size and power calculation

The sample size calculation is based on the primary endpoint of the study, a difference in the ODI 2 years post intervention [8]. The sample size was calculated based on the two-group *t* test (GraphPad StatMate Software, version 2.0). Based on a minimally clinical important change of 10% on the ODI, standard deviation for the ODI of 20%, significance level of *p* ≤ 0.05, and power of 80%, an estimated 64 patients are required in each of the intervention groups, for the primary endpoint. The current sample size of 154 patients allows for a 20% loss to follow up while maintaining > 80% statistical power [23].

### Statistical analysis

Primary and secondary variables and their change from baseline will be summarized by treatment group. Endpoints will be analyzed as appropriate in dependence on the data distribution at a two-sided 0.05 level of significance. Detailed descriptive statistics will be provided for the data collected and 95% confidence intervals will be calculated for all relevant estimates. Measurements on the course of follow up will be analyzed by analysis of covariance (ANCOVA) or generalized model alternatives for categorical or semi-quantitative data. Additional covariates, such as baseline measurements, will be included in the model as appropriate. MRI parameters and variables to assess functional neurological status will be summarized descriptively. Imputation of missing data has not been planned. The primary analysis will follow as randomized. All values will be expressed as the mean and standard deviation.

Data are analyzed for normality by the Kolmogorov-Smirnov test. The Wilcoxon signed-rank test or the paired *t* test is used to analyze continuous paired data, while McNemar’s test is used for categorical data. The Mann-Whitney U test and unpaired *t* test, are used to perform group comparisons of continuous clinical outcome variables while the chi-square and Fisher’s exact test are used to analyze intergroup differences in categorized outcome variables and demographic characteristics (age, sex ratio, duration of symptoms, etc.), respectively. Statistical analysis will be performed after recruitment, one year postoperatively and after completion of the last visit of the study population at the specified time points. An interim analysis will be performed 6 and 12 months after recruitment and after completion of the last visit of the study population at the specified time points.

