## Methods/design

### Study design

The mPACT study is a single-center, randomized, controlled, parallel group, superiority trial with 154 patients allocated to the groups in a 1:1 ratio. Any trial involving a surgical procedure precludes surgical investigators from being blinded. Patients, however, will be blinded to the randomized treatment and further evaluations, such as radiologic analyses, will be conducted in a blinded fashion whenever possible. The expected enrollment time is 2 years. The conclusion of the study is estimated 5 years thereafter. The primary study endpoint is the difference in Oswestry Disability Index (ODI) between treatment groups at 2 years after surgery. The ODI is a widely used tool for the assessment of therapeutic effect. It consists of ten sections, with six questions in each section. A lower score indicates a higher level of function. An overall score of all 10 sections of the ODI will be computed and used as the ODI score. The standardized version of the ODI can be computed by re-scaling the score to the range 0–100 [8]. Moreover, the generic health status is assessed with the EuroQoL 5-Dimension questionnaire (EQ-5D) [9]. The Beck Depression Inventory (BDI) is used as a multiple choice self-reported inventory for measuring the severity of depression and responsiveness to treatment [10]. To identify neuropathic pain components the painDETECT questionnaire (PD-Q) will be used [11]. Furthermore, with the “timed up and go” (TUG) test the physical ability of walking is objectively documented and quantified [12]. Preoperative and postoperative magnetic resonance imaging (MRI) of the lumbar spine is performed. The image protocols include sagittal and axial sequences, both T1 and T2 weighted, in all patients [13–17]. A computed tomography (CT) scan is routinely performed one year after the intervention to assess the overall fusion rate [18]. Pre-operative American Society of Anesthesiologists (ASA) grade staging might allow the identification of risk factors. Neurological status and the quality and quantity of current pain medication are documented. Operation time and time of hospitalization is recorded. Pain medication usage, including epidural injections and nerve block injections are documented. Quantitative sensory testing (QST) is performed to assess and quantify low back pain non-invasively [19]. Blood samples will be tested preoperatively and postoperatively for TNF-α, IL-6, C-reactive protein (CRP) and leukocytes [20]. Direct costs of hospital care and the indirect costs of follow-up treatment outside the hospital will be evaluated. Costs of surgery and hospitalization including duration of inpatient stay, costs of nursing, costs of medication and physiotherapy are assessed after discharge from the hospital, according to the hospital’s internal cost-estimate lists. Additionally, the indirect costs after hospital discharge including physiotherapy, rehabilitation centers, pain medications, medical consulting etc. are documented on a routing sheet. Postoperative care is not standardized in the study protocol and will be performed according to the standard of care for degenerative lumbar spondylolisthesis at the study site. Primary and secondary outcome parameters are outlined in more detail in Table 1. Ethics approval was attained at the local ethics committee. This study complies with the World Medical Association Declaration of Helsinki Ethical Principles for Medical Research Involving Human Subjects, 2008. The final report will follow the CONSORT 2010 guidelines and its extension to non-pharmacological interventions. The CONSORT checklist is attached as Additional file 1.

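### No single analysis is fixed for the primary 2-year ODI comparison: the method is left to the data distribution, so the reported quantity can change and baseline ODI may go unused

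*Protocol article*

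**What the plan says.** All references are to the protocol article.

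- **Endpoint (Study design):** "The primary study endpoint is the difference in Oswestry Disability Index (ODI) between treatment groups at 2 years after surgery".
- **Sizing (Sample size and power calculation):** "The sample size was calculated based on the two-group" t test, for a difference of 10% with an SD of 20% on the ODI. This is a difference in means without baseline adjustment.
- **General rule (Statistical analysis):** "Endpoints will be analyzed as appropriate in dependence on the data distribution at a two-sided 0.05 level of significance".
- **Normality check (same section):** "Data are analyzed for normality by the Kolmogorov-Smirnov test".
- **Unadjusted candidates (same section):** "The Mann-Whitney U test and unpaired *t* test, are used to perform group comparisons of continuous clinical outcome variables".
- **Model candidate (same section):** "Measurements on the course of follow up will be analyzed by analysis of covariance (ANCOVA) or generalized model alternatives" for categorical or semi-quantitative data. Baseline values are an example of covariates to be added where judged appropriate.

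The same section says that the primary analysis goes by randomized group. That settles which patients are compared and in which arm, but not the test or model.

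**The concern.** The 2-year ODI is both a continuous clinical outcome and a follow-up measurement, so both method sentences cover it. Three analyses are therefore open for the one confirmatory comparison: t test, Mann-Whitney U and ANCOVA. The only stated guide is the distribution of the outcome data.

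Three things are at stake.

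1. **What is estimated.** The t test and ANCOVA address a mean difference in ODI points, the scale on which the 10-point target is set. Mann-Whitney addresses whether values in one arm tend to exceed those in the other. The two coincide only in special cases, such as a pure shift of the whole distribution.
2. **Freedom of choice.** Adjusted and unadjusted analyses of the same data can fall on opposite sides of 0.05, and the text does not say which one counts.
3. **Precision.** Both unadjusted tests discard baseline ODI. The trial evidently collects it, because changes from baseline in the primary variable are to be summarised.

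**Working it through.** **Inputs from the article:** difference 10, SD 20, two-sided 0.05, power 80%, 154 patients allocated 1:1, 20% loss. **Not in the article, so assumed:** the correlation r between baseline and 2-year ODI.

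**1. The plan's own figure.** The normal approximation is n = 2(1.960 + 0.842)² × 20² / 10² = 62.8, so 63 per arm. The exact two-sample t test gives 63.77, rounded up to 64, with 80.1% power at 64. The stated 64 per arm is reproduced, and it rests on an unadjusted comparison of means.

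**2. Evaluable patients.** 154 × 0.8 / 2 = 61.6 per arm.

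**3. Power of the unadjusted tests there.** With d = 10/20 = 0.5, the t test has 78.6%. For normal data Mann-Whitney has relative efficiency 0.955, so it acts like 0.955 × 61.6 = 58.8 per arm and has 76.7%.

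**4. Power of ANCOVA.** The residual SD is 20√(1 − r²). The standard error of the difference is that SD × √(2/61.6). The equivalent gain in patients is 1/(1 − r²) − 1.

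| r (assumed) | residual SD | SE, ODI points | power at 61.6 per arm | n per arm for 80% | equivalent extra patients |
|---|---|---|---|---|---|
| 0 | 20.00 | 3.60 | 78.6% | 64 | 0% |
| 0.2 | 19.60 | 3.53 | 80.2% | 62 | 4% |
| 0.3 | 19.08 | 3.44 | 82.3% | 59 | 10% |
| 0.4 | 18.33 | 3.30 | 85.2% | 54 | 19% |
| 0.5 | 17.32 | 3.12 | 88.9% | 49 | 33% |

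**5. Does the two-step rule inflate the type I error?** Simulation used 62 per arm, 4,000 replicates and assumed r = 0.5. The Kolmogorov-Smirnov test was applied in each arm with estimated mean and SD, and Mann-Whitney was used if either arm gave p < 0.05. The skewed case was a gamma distribution with shape 1.6 and SD 20.

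| no true difference | normal data | skewed data |
|---|---|---|
| t test alone | 5.4% | 5.0% |
| two-step rule | 5.4% | 5.4% |
| switched to Mann-Whitney | 0.05% of replicates | 33% of replicates |
| smallest p of t test, Mann-Whitney and ANCOVA | 8.7% | 8.5% |

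The Monte Carlo standard error is √(0.05 × 0.95 / 4000) = 0.34 points, so 5.4% is little more than one standard error from 5%. A second simulation of the two-step rule gave 4.9% (normal) and 4.8% (skewed). A further run of 10,000 replicates with normal data put the smallest-of-three figure at 7.1% for r = 0.3 and 8.0% for r = 0.5.

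The two-step rule is therefore close to nominal. What it does change is the quantity reported, in about a third of replicates under this skewed shape.

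**The case against.** - **The text does not literally make the normality test a gate.** This is correct. The paragraph with the Kolmogorov-Smirnov test is a general list that also covers paired data, categorical data and demographics. The gate is inferred from the distribution-dependent rule, the normality check and the parametric and nonparametric pair. It is the natural reading but should be called a reading.
- **ANCOVA may be meant only for repeated visits, with the t test implied by the sample-size section.** This is possible. On that reading the choice between t test and Mann-Whitney remains, and baseline ODI is left out of the primary comparison. On the other reading three analyses compete. Either way the text needs repair.
- **A reader might infer that the two-step testing breaks the 5% level.** The calculations do not support this. The figures of 7.1% to 8.7% arise only if the most favourable of three p-values is reported, and nothing in the article plans that. They measure the freedom left open, not the stated procedure.
- **An unadjusted t test is valid after randomization, and baseline covariates are provided for.** Both are true. Adjustment is a gain in efficiency, not the correction of an error. The article makes it optional.
- **Mann-Whitney can be the more powerful test.** In the skewed simulation with a 10-point shift it reached 93.2%, against 89.0% for ANCOVA and 81.2% for the t test. That supports keeping it as a sensitivity analysis. It does not make it an estimate of the mean difference.
- **Detail may sit in an analysis plan that is not shown.** Covariate lists and standard-error methods can. But the article is not silent here: it writes in a distribution-dependent rule and rival methods, which an analysis plan would have to override. Its commitment to means, SDs and 95% confidence intervals softens the problem but does not say which comparison is primary.

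**Conclusion.** The point stands in a limited form. The Statistical analysis section makes the method depend on the data and names no single analysis for the 2-year ODI, although the trial was sized on a difference in means. The harms are a target that can change with the data, an open choice between adjusted and unadjusted results, and possible loss of precision. Type I error inflation from the two-step rule is not among them. Nor does the sample size call for a normality gate: with about 62 per arm, a comparison of means does not need normally distributed data.

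On the stated inputs alone, t test and Mann-Whitney differ by about 2 points of power for normal data (78.6% against 76.7%). The larger figures, about 82%, 85% and 89% for ANCOVA, hold only if r is 0.3, 0.4 or 0.5, and the article gives no value. It would go too far to say that ANCOVA is certain to restore the stated power of more than 80%: at r = 0 it stays at 78.6%, and at r = 0.2 it reaches only 80.2%. That 154 patients with 20% loss fall short of the stated power under the unadjusted t test is a separate sample-size point and adds no weight here.

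**What to change.** State one primary analysis, before any 2-year ODI data are compared by arm. Suggested wording:

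*The primary analysis is an ANCOVA of ODI at 2 years (0–100 scale) on treatment and baseline ODI. The adjusted mean difference with its 95% confidence interval is reported whatever any normality test shows. A Mann-Whitney U test is a sensitivity analysis only.*

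Exempt the primary endpoint from the distribution-dependent rule and from the Kolmogorov-Smirnov check. Those provisions can stay for secondary and descriptive comparisons if wanted.

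The cost is two or three sentences, with no new data and a method that the article already lists. One practical consequence should be covered: no imputation is planned, so a patient without a baseline ODI would drop out of the model unless the plan says how that case is handled.

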
**Table 1 Tab1:** Primary and secondary outcome parameters

Outcome parameters	Assessments
Primary outcome parameter	Oswestry Disability Index (ODI) at 2-year follow up to measure degenerative lumbar spondylolisthesis-related disability [8]
Secondary outcome parameter	Questionnaire - Timed “Up and Go” test (TUG) [12] - Beck depression inventory (BDI) [10] - Changes in physical and mental health captured by the Short Form (SF)-12v2 [9] - Core outcome measure index (COMI) [30, 31], patient-orientated outcome questionnaire including - visual analog scale (VAS) for back and leg pain - patient’s satisfaction - work disability - social disability - Pain relief on 100-mm VAS for back pain and leg pain - PainDetect Questionnaire (PD-Q) [11] - EuroQoL 5-Dimension (EQ-5D) [9]
	Intraoperative - loss of blood (LOB) - amount of blood transfusion - operative time - length of wound incision - type of wound closure
	Various - duration of hospitalization - device-related complications - surgery-related complications - re-operations - adverse events (AE), severe adverse events (SAE)
	Health care contacts
	Pain medication usage
	Hospital costs
	Radiological evaluation - MRI [13–16, 32] - x-ray evaluation (antero-posterior, lateral, flexion and extension, standing for overall sagittal alignment and differences in lordosis) - CT scan (overall fusion rate, rate of radiological and/or symptomatic adjacent segment disease, rate of pedicle and/or cage system implant failures)
	Serum markers (CRP, leukocytes, TNF-α, IL-6)

The primary study endpoint is the difference in Oswestry Disability Index between treatment groups at 2 years after surgery

*MRI* magnetic resonance imaging, *CT* computed tomography, *CRP* C-reactive protein

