### Study population

The mPACT trial will include patients with lumbar degenerative spondylolisthesis of Meyerding grade I or II, who qualify for decompression and fusion of ≤ 3 lumbar spinal levels by a posterior medialized cortical bone trajectory or by a traditional trajectory for lumbar pedicle screw placement. These participants need to have failed adequate conservative or interventional therapy for a minimum of 3 months. Additionally, radiologically determined pathologic change at the treatment level needs to correlate with the primary symptoms. Patients with significant morbidities need to be excluded as this may lead to differences in treatment efficacy. Inclusion and exclusion criteria are described in detail in Table 2. Informed consent is obtained from each patient.

**Table 2 Tab2:** Inclusion and exclusion criteria

	Criteria
Initial inclusion criteria	Age between 18 and 85 years Clinical signs of low back pain and/or radiculopathy from vertebrae L1 to S1 MRI and CT confirmed: central canal stenosis, lateral recesses stenosis, or foraminal stenosis leading to: - radiculopathy, defined as pain and/or motor weakness or paralysis and/or paraesthesia in at least one specific nerve root distribution from vertebrae L1 to S1 or - neurogenic intermittent claudication, defined as pain and/or weakness and/or abnormal sensation in the legs during walking or prolonged standing or - indicating decompressive surgery and instrumented mono-segmental, bi-segmental or tri-segmental spondylodesis with posterior instrumented fusion system and an intervertebral cage (TLIF) Unresponsive to non-operative treatment for a minimum of 3 months including at least physiotherapy, pain medication and local infiltration therapy Presence of progressive symptoms or signs of nerve root and/or spinal cord compression although performing conservative treatment Psychosocial, mental and physical ability to understand and to perform with this protocol, especially visiting scheduled follow-up controls, observe treatment plan and all other study-related procedures Personally signed and dated informed consent document prior to any study-related procedures indicating that the patient has been informed of all pertinent aspects of the trial

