## Discussion

The high prevalence of spinal disease, especially the increasing number of patients with degenerative disc disease, extensively increases the demand for spinal fusion surgery [26]. The standard surgical technique used is pedicle screw fixation with transforaminal lumbar interbody fusion [1]. Although it is an established technique, it is nevertheless an invasive intervention with high complication rates that appear to increase with age, blood loss, operative time, and the number of levels treated [2]. Therefore, minimally invasive techniques have been developed to minimize tissue damage, reduce blood loss, decrease narcotic requirement, and shorten the length of hospital stay [27]. The mPACT technique was established as one of these techniques. A posterior lumbar interbody fusion (PLIF) is then additionally used to perform an intervertebral fusion [6]. However, the PLIF is associated with higher rates of nerve tissue damage and extends the duration of operative procedure in comparison with TLIF [28]. In our prospective, clinical, randomized, controlled trial we will thus use TLIF only.

Implant loosening, especially in patients with poor bone nutrition, is another mentionable drawback that may be associated with spinal instrumentation [29]. The mPACT technique offers greater cortical bone contact [3] and therefore shows several promising advantages in biomechanical testing in comparison to traditional pedicle screw fixation. The cortical bone trajectory increases the pullout strength and improves the rigidity of spinal instrumentation [4].

Most clinical data on this subject are based on retrospective investigations or small prospective cohort studies without long-term results [3, 6, 7]. At this time, there are no prospective, clinical, randomized, controlled trials available. With current standards, well-validated outcome instruments are mandatory to provide efficient surgical treatment recommendations for patients with lumbar degenerative disc disease. This trial will contribute to the understanding of the short-term and long-term clinical and radiological postoperative course in patients with lumbar degenerative disc disease in which the mPACT technique is used.

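### One-time perioperative outcomes are compared with covariate-free tests across fusions of differing extent and ages 18 to 85; the tests are valid but probably give up some precision

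*Protocol article*

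**What the plan says.** Statistical analysis in the protocol article has two strands.

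- **Two-group tests.** For continuous outcomes, the Mann-Whitney U test and the unpaired t test "are used to perform group comparisons of continuous clinical outcome variables". For categorical ones, the chi-square test and "Fisher’s exact test are used to analyze intergroup differences in categorized outcome variables and demographic characteristics".
- **Models.** "Measurements on the course of follow up will be analyzed by analysis of covariance (ANCOVA) or generalized model alternatives for categorical or semi-quantitative data". On covariates: "Additional covariates, such as baseline measurements, will be included in the model as appropriate". Baseline measurements are the only example; neither number of levels nor age is named.

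Table 1 lists, under intraoperative outcomes, "loss of blood (LOB) - amount of blood transfusion - operative time - length of wound incision", and places duration of hospitalization under various outcomes.

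Study population admits patients "who qualify for decompression and fusion of ≤ 3 lumbar spinal levels", and the inclusion part of Table 2 allows "mono-segmental, bi-segmental or tri-segmental spondylodesis with posterior instrumented fusion system". The radiological exclusion criteria in the same table rule out patients who need surgery at three or more lumbar levels. The age range is 18 to 85.

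The Discussion describes fusion as having "high complication rates that appear to increase with age, blood loss, operative time, and the number of levels treated". The Randomization section gives an allocation command containing `strata(2)` and does not name the stratifying variable.

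**The concern.** Operative time, blood loss, incision length and stay are recorded once and have no preoperative value, so they are not naturally measurements over the course of follow-up. Read as written, the plan sends them to tests that take no covariate. If a longer fusion takes more time, bleeds more and keeps patients in longer, the spread between one-level and multi-level operations goes into the error term and widens the interval for the technique effect.

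The Discussion gives less tissue damage, less blood loss and a shorter stay as the reasons for minimally invasive techniques, so these secondary outcomes carry much of the argument for mPACT. The number of segments to be fused is part of the eligibility assessment and age is known at entry, so both can be fixed before allocation. Leaving them out would discard information that the trial already has to collect.

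**Working it through.** **The plan's own figure.** Difference 10, SD 20, two-sided 0.05, power 80%: the normal approximation gives 63 per arm and the t test 63.77, so the stated 64 per arm is reproduced. It concerns the ODI only. The article gives no SD, effect or sample size reasoning for the perioperative outcomes.

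**Inputs.** From the article: 154 patients at 1:1, so 77 per arm; two-sided 0.05. Assumed, because the article does not give them: the mix of levels, and k, the shift in outcome per added level in within-level SDs. Age is left out of the arithmetic; its contribution is unknown.

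**Formulas.**
- Share of variance explained by levels: R² = k²V / (1 + k²V), where V is the variance of the number of levels.
- Ratio of adjusted to unadjusted interval width: √(1 − R²).
- Equivalent multiple of the sample size: 1 / (1 − R²) = 1 + k²V.

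For a 70/30 mix of one and two levels, V = 0.7 × 0.3 = 0.21. For 60/40, V = 0.24. For 60/30/10 with one, two and three levels, V = 2.7 − 1.5² = 0.45.

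| Mix | k | R² | Interval narrower by | Equivalent N |
|---|---|---|---|---|
| 70/30 | 0.25 | 0.013 | 0.7% | × 1.01 |
| 70/30 | 0.5 | 0.050 | 2.5% | × 1.05 |
| 70/30 | 1.0 | 0.174 | 9.1% | × 1.21 |
| 70/30 | 1.5 | 0.321 | 17.6% | × 1.47 |
| 60/40 | 0.5 | 0.057 | 2.9% | × 1.06 |
| 60/40 | 1.0 | 0.194 | 10.2% | × 1.24 |
| 60/30/10 | 0.5 | 0.101 | 5.2% | × 1.11 |
| 60/30/10 | 1.0 | 0.310 | 17.0% | × 1.45 |
| 60/30/10 | 1.5 | 0.503 | 29.5% | × 2.01 |

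With one- and two-level cases only, V cannot exceed 0.25. At k = 1.5 the gain is then at most 1 − 1/√(1 + 2.25 × 0.25) = 20%. Over this range of k, anything larger needs three-level cases.

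**In terms of power.** At 77 per arm the unadjusted detectable difference at 80% power is (1.960 + 0.842) × √(2/77) = 0.452 SD. It falls to 0.440 at R² = 0.05, 0.404 at 0.20 and 0.378 at 0.30. For a true effect of 0.4 SD, power is 69% unadjusted, 77% at R² = 0.17 and 84% at R² = 0.31.

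**Validity check.** In a simulation of 154 patients with the 60/30/10 mix (1,500 runs per scenario), type I error was 4.6% to 5.8% across both methods. With a true effect of 0.45 within-level SD, power was 75% unadjusted against 78% adjusted at k = 0.5, and 62% against 78% at k = 1.0.

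**Cost of useless covariates.** Two terms that predict nothing raise the variance by about 2/(154 − 2 − 3) = 1.3%, or 0.7% in standard error. At k = 0.25 with a 70/30 mix this cancels the gain.

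**Complications.** With the 60/30/10 mix and assumed rates by level of 10/15/25% or 10/20/35%, R² is 0.019 or 0.048. The standard error of the risk difference falls by only about 1% to 2.5%.

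**The case against.** The strongest reply is that nothing here is an error. All four named tests are valid under 1:1 randomization, the outcomes are secondary, and covariate lists for secondary outcomes commonly go into an analysis plan that is not at hand. The article also says that endpoints will be analysed as the data distribution requires, and it allows models with covariates as appropriate. Validity stands in full. The appeal to the analysis plan stands in part: adjustment is not forbidden. But the article does assign a test to continuous group comparisons and reserves the models for follow-up measurements, so for the four one-time outcomes the default is stated, not left open.

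A second reply is that the article's evidence and the possible gain do not meet. The Discussion links levels and age to complication rates, where the gain is smallest. For operative time, blood loss, incision length and stay, the link is an inference. This stands, and it is why the size is given only under assumptions.

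Three stronger readings are tempting, and the article does not support them:

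- **Chance imbalance in levels biases the comparison.** With 30% two-level cases, the standard error of the difference in their share between arms is √(2 × 0.21/77) = 7.4 percentage points, so noticeable imbalance is ordinary. The unadjusted standard error already allows for it. If `strata(2)` refers to levels, imbalance is also limited by design.
- **Complications are locked into unadjusted tests.** Those arising during follow-up can fall under the generalized-model sentence, and regression may be unstable if events are few.
- **The ODI analysis is deficient for the same reason.** Nothing in the article ties levels or age to the ODI, and baseline adjustment is already foreseen there.

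**Conclusion.** The point holds as a modest efficiency concern, confined to operative time, blood loss, incision length and hospital stay. The planned comparisons are valid and unbiased; they are probably less precise than they could be at almost no cost.

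The loss cannot be derived from the article. It rests on the assumed mix and per-level shift: about 2.5% to 18% in interval width for 70/30 and 0.5 to 1.5 within-level SDs, nothing worth having at 0.25 SD, and up to about 30% only if three-level cases are enrolled. Whether they may be enrolled is unclear, because the inclusion text and the radiological exclusion contradict each other. The point survives either resolution, since one- and two-level fusions are pooled in any case. The primary ODI comparison and its sample size are unaffected.

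**What to change.** 1. For operative time, blood loss, incision length and hospital stay, prespecify a linear model (on the log scale where the outcome is skewed) with arm, planned number of levels and age. Use the number of levels planned and recorded before allocation, not the number finally fused, which may depend on the operation itself.
2. State which variable lies behind `strata(2)`, and add it to the model if it is not already there.
3. Keep the unpaired t or Mann-Whitney comparison as a sensitivity analysis.
4. Reconcile the inclusion text and the radiological exclusion on three-level cases.
5. Adjust complications for the same terms only where event counts allow; this is optional. No change to the ODI model is asked for on this ground.

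The cost is a short change of wording, a few extra model terms (about 0.7% in standard error if both covariates prove useless), and making sure that the planned number of levels is entered before allocation. The model also yields an adjusted estimate with the 95% confidence interval that the article promises for relevant estimates.
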